### Data analysis

In all relevant cases, additional analyses, including interaction effects and subsample differences, will be examined. **Data analyses related to objective ****1**(i.e., determining the extent of thorough SSE performance defined in terms of frequency and completeness): Descriptive and inferential statistics will be employed to gain a differential picture of patients’ practice of SSE in terms of completeness and frequency at T3 and T4 for the total sample as well as for subsamples according to sex, age, having a partner, etc. **Data analyses related to objective ****2** (i.e., identifying psychosocial variables independently associated with thorough SSE): First, hierarchical multiple regressions will be performed with SSE completeness as dependent variable using T3 data, i.e., 3 months after standardized dermatological education. The independent variables described above will be entered block-wise, i.e., 1^st^ block: sex; 2^nd^: skin cancer knowledge, attitude toward SEE; 3^rd^: self-efficacy for performing SSE; 4^th^: skin cancer-specific distress measure; 5^th^: partner support and physician support; 6^th^: total score of the coping measure (note that analyses will be repeated with the individual coping subscales). Second, a multinomial regression will be conducted with the same predictor variables and SSE frequency (i.e., too low, ideal and too high frequency) as the dependent variable. The strategies described for T3 will be repeated using the data collected at T4, i.e., 12 months after the education session. With the projected sample size of N = 200, a minimal R^2^ increment of .08 will be detected with .79 power. The power for detecting a R^2^ increment of .09 will be .85. The variance explained by both blocks and individual variables will be examined. The two dependent variables are treated separately because they reflect different aspects of SSE practice. As a second step, they may also be clustered and the resulting composite measure of SSE behavior will serve as the dependent variable in regressions similar to the ones described above. **Data analyses related to objective ****3**(using qualitative methods for an in-depth understanding of psychosocial factors related to SSE): Data saturation in qualitative theme analysis, depending on the level of structure of the interview, is often achieved with a sample of 10–15 participants who are examined intensively, while larger samples typically add only minimal new data [131]. Consensual Qualitative Research [131-133] will be applied to the semi-structured interviews of 15 male and 15 female patients. This qualitative method is based on principles of grounded theory [134] and aims at developing a theory directly grounded in the phenomena under study. As a first step, the 2 independent sets of interviews will be theme analyzed to establish preliminary categorizations through open coding. To guide this, the following preliminary questions will be used: how do patients cognitively, affectively and behaviorally adjust to cancer diagnosis and treatment?; how and why do patients engage in or refrain from performing SSE?; how do they experience practicing SSE (e.g., does SSE evoke discomfort, does it trigger tumor fear, does it lead to a sense of safety and control?); in which ways do significant others support or undermine SSE practice?; do patients find it hard to ask significant others for help with SSE or do patients feel overwhelmed by a others’ motivation to help?; and in which ways are physicians experienced as helpful or as non-supportive? Axial coding will then be conducted by which open codes are reviewed and synthesized. As a final step, selective coding will be conducted in order to articulate theories derived from the data and establish the inter-relations between the constructs that were found. By definition, Consensual Qualitative Research is conducted independently by two raters, who then meet to discuss their coding until a consensus is reached. A third independent rater will be available to address disagreements. All proposals are then edited by an editor.

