During regular clinic visits up to 12 months after their melanoma diagnosis, i.e., at time 1 (T1), eligible patients will be advised by the clinical care staff about the opportunity to participate in the study. In addition, the study will be advertised through flyers and posters in the waiting room area, which will allow interested patients to proactively contact the research team about study participation. The research assistant will provide study information to interested patients, verify study eligibility and collect written, informed consent. Participants will be asked to complete baseline questionnaires on sociodemographic and illness-related information, past SSE behaviors, and psychological functioning at the clinic. Alternatively participants can complete the questionnaires at home and return them to the research team by mail. The research assistant (RA) will access the participants’ medical charts in order to complete the medical information sheet. The second assessment will take place in conjunction with the delivery of the dermatological education at the clinic 3 to 6 months after T1, i.e., at time 2 (T2). Participants will complete questionnaires about distress, coping strategies, physician support and about SSE knowledge, attitude, and self-efficacy. In addition, participants who, at the time of data collection, report having a spouse (i.e., having a committed intimate relationship), will be asked to answer questions related to their partner’s impact on SSE practice. Furthermore, these patients will be asked to take home a survey for their spouse, which mirrors the partner-related questions that the patient is asked to answer regarding SSE. Also at time 2, all study participants will receive a 20-minute standardized dermatological education on SSE derived from empirical evidence [14,29,47,50,65,98-104] and best practice guidelines [36,38,105-109]. Patients will be encouraged to attend the education session together with a significant other (e.g., spouse, other family member, friend) who could assist them with SSE. During the education session, the dermatology-trained RA, i.e., the health educator, will emphasize the usefulness of monthly whole body exams as an effective measure to detect suspicious skin lesions as early as possible. The educator will provide detailed information about how to conduct an effective SSE. This will include an explanation of the well-established ABCDE paradigm (lesion Asymmetry; Border irregularity; Color variation; Diameter; Evolution, e.g. change in size, shape, symptoms, etc.) [110-113] for the detection and interpretation of pigmented lesions by lay persons and health care professionals. Furthermore, the educator will provide handouts, which will assist participants with regular SSE, including a summarizing brochure on melanoma [114], a bookmark with color printed examples of lesions [111], a leaflet providing the link to an online video modeling skin self-examination [115], and a SSE Journal to record skin spots of concern and body parts covered during each home SSE [116,117]. At the end of this 20-minute session, the educator will encourage the participant to reflect on their SSE intentions. Subsequently the participant will be asked to note down in the SSE journal *if*, *when*, *where*, and *assisted by whom* the participant plans to conduct self-exams. At time 3 (T3), i.e., 3 months after the dermatological education, participants are invited by letter to fill out questionnaires assessing distress, coping strategies, physician and spousal support as well as SSE knowledge, attitude, and self-efficacy. In addition, a 10-minute, structured SSE behavior interview with the RA will be scheduled for T3 to assess practice of SSE over the last 3 months. At time 4 (T4), 12 months after the dermatological education, participants will be invited by letter to complete an assessment identical to T3, i.e., questionnaires and SSE behavior interview. At T4 a subsample of 30 patients, which will include the first 15 men and the first 15 women who consent to participate, will be invited to take part in a 50-minute individual, semi-structured interview based on the McGill Illness Narrative Interview [118] focusing on the following questions: 1) how patients deal with the diagnosis and how they experience the illness; 2) their experience regarding SSE, including how they deal with the ongoing need for thorough SSEs and obstacles to SSE; 3) their experience of physician support of SSE, or lack thereof, and how they deal with it; and 4) their experience of partner support of SSE, or lack thereof, and what facilitates or hinders partner support and how they deal with it. Biological sex is considered explicitly given that previous melanoma research suggests that this is a key variable in relation to SSE [27,45,119-121]. Participants will be invited to share and report their thoughts, feelings, and behaviors in each of the 4 domains, which were selected based on their relevance to the cancer trajectory and their presumed significance for SSE practice.

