
### Measures

#### Descriptive and independent variables: predictors of skin self-examination

Study measures were selected based on their wide use in cancer research, on their psychometric properties, and on their direct relevance to the objectives of the project. They are used to assess descriptive and independent variables, which are expected to have an effect on SSE behaviors during the first 3 months (T1) and 12 months (T2) after dermatological education.

The Sociodemographic Information Form [67] includes questions about age, sex, education, having a spouse, socioeconomic status, and cancer diagnosis. With the Medical Information Sheet [30] the RA gathers data such as time since diagnosis, melanoma stage and depth, previous diagnosis of cancer, melanoma treatment and disease progression. The Skin Cancer Prevention Scale [122] captures whether patients performed SSE and have been advised by health care providers about SSE prior to their current melanoma diagnosis. The Skin Cancer Knowledge Scale, based on questionnaires by Hay et al. 2006 [65] and Manne et al. 2006 [45], assesses knowledge regarding melanoma risk, melanoma warning signs and SSE. The SSE Attitude Scale, an adaptation of Manne’s SSE Benefits and Barriers Scale [45], assesses perceptions of SSE importance, personal gain through SSE, and barriers to SSE. The SSE Self-Efficacy Scale, based on Weinstock et al. 2007 [123], captures an individual’s self-confidence in performing effective skin self-exams. The Physician SSE Support Scale [124] inquires about the perceived interest that the treating physician conveys regarding the patient’s practice of SSE. The Berlin Social Support Scale [125] assesses the patient’s perception of emotional, instrumental and informational illness support provided by their spouse (patient perception and partner perception). The Skin Cancer Index [126,127] is a self-report scale focusing on emotional, social and appearance-related concerns associated with skin cancer. The Patient Health Questionnaire, PHQ-4, [128] screens for symptoms of depression and anxiety. The COPE Inventory [129] inquires about an individual’s use of coping strategies, e.g., mental disengagement, behavioral disengagement, focus on and venting of emotions, use of instrumental social support, denial, humor, use of emotional social support, planning and others.

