#### Dependent variables: skin self-examination

Adherence to medical advice on SSE is assessed at 3 months (T3) and at 12 months (T4) after the standardized education session. Based on prior SSE research [30,45,58] and on recommendations for a monthly, comprehensive skin self-exam from the Canadian Dermatology Association [130], the American Academy of Dermatology [108] and the American Cancer Society [38], a structured SSE-behavior interview was developed and pilot tested [30]. During this 10-minute interview the RA records SSE behaviors in terms of SSE completeness and frequency. With the help of a calendar and the body map, which participants receive during the education session in order to document each SSE at home, SSE is recorded for five specified areas of the body: 1) head and neck; 2) front upper body including arms and shoulders; 3) front lower body including groin/genital area, legs, and feet; 4) back upper body including lower back; 5) back lower body including buttocks *and* back of legs. SSE assistance by significant others and the use of melanoma pictures during the self-exams will be documented. The first dependent variable, C*ompleteness of SSE*, refers to the examination of the 5 body areas mentioned above. The RA inquires about each of these 5 parts of the body for each skin self-exam reported by the patient over the last three months at T3 and at T4. The interviewer gives one point for each body area examined, for a possible total of 5 points reflecting the completeness, in regards to the 5 body areas, of each SSE conducted. A mean score (on 5) is calculated across all SSEs. The second dependent variable is *Frequency of SSE* over a given time period. Over the period of 3 months covered by the assessment at T3 and at T4, ideal frequency would be 3 SSEs, with more than 3 SSEs reflecting too high a frequency, and less than 3 reflecting too low a frequency. The total count of SSEs (i.e., how many times a patient performed a SSE) over 3 months will be used to determine if the frequency with which an individual patient conducted SSEs was too low, ideal or too high, which will be used for the data analysis.

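### As most naturally read, the objective 2 models take their psychosocial predictors from the same wave as the outcome, at or after the end of the three months of behaviour to be predicted

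*Protocol article*

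**What the plan says.** All references are to the Protocol article.

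- **Models.** Data analysis states that "hierarchical multiple regressions will be performed with SSE completeness as dependent variable using T3 data". It continues: "The independent variables described above will be entered block-wise", and lists six blocks: sex; knowledge and attitude; self-efficacy; skin cancer-specific distress; partner and physician support; coping. A multinomial model for frequency uses the same predictors. Then: "The strategies described for T3 will be repeated using the data collected at T4".
- **Outcome window.** Participants and procedures describes a "structured SSE behavior interview with the RA will be scheduled for T3 to assess practice of SSE over the last 3 months". The section on dependent variables confirms the same look-back at both waves: the five body areas are asked about "for each skin self-exam reported by the patient over the last three months at T3 and at T4".
- **Predictor scales at T3 and T4.** Three months after the education session, participants are invited by letter to "fill out questionnaires assessing distress, coping strategies, physician and spousal support as well as SSE knowledge, attitude, and self-efficacy". T4 is described as identical to T3.
- **Predictor scales at T2.** At the education visit, "Participants will complete questionnaires about distress, coping strategies, physician support and about SSE knowledge, attitude, and self-efficacy". Those with a spouse also answer partner questions.
- **Aim.** The main objective is to identify short- and long-term predictors. Hypothesis 2 says that psychosocial variables will predict additional variance. The Discussion expects to explain which factors affect the acquisition and maintenance of self-examination.

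**The concern.** If blocks 2 to 6 come from T3 for the T3 outcome and from T4 for the T4 outcome, the time order runs the wrong way. The behaviour fills the three months before the interview, and the scores are taken when that window closes. They may come later still, because questionnaires completed at home can be requested up to three times.

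Self-efficacy and knowledge may rise because a patient has practised. Distress may rise or fall with what the exams turn up. Reported partner support may reflect help already given. The article allows for this itself: its qualitative questions ask whether self-examination triggers fear or brings a sense of safety and control.

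A same-wave coefficient mixes the two directions. The findings are meant to guide the design of a tailored psychosocial intervention, so a factor that is partly a consequence of self-examination could be chosen as a target for changing it.

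**Working it through.** **1. Time order, from Participants and procedures and Measures**

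| Wave | Timing | Predictor scales | Outcome window |
|---|---|---|---|
| T1 | up to 12 months after diagnosis | baseline psychological functioning; past self-examination | none |
| T2 | 3 to 6 months after T1, at the education visit | distress, coping, physician support, knowledge, attitude, self-efficacy; partner questions if there is a spouse | none |
| T3 | 3 months after education | same constructs | months 0 to 3 |
| T4 | 12 months after education | same constructs | months 9 to 12 |

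For the T3 outcome, only T2 scores come before the window. For the T4 outcome, both T2 and T3 scores do. Sex (block 1) does not change with wave, so the point concerns blocks 2 to 6.

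**2. The plan's own figures**

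The article gives power of .79 for an R² increment of .08 and .85 for .09 at N = 200. It does not give alpha, the number of predictors tested or the R² of earlier blocks, so these cannot be reproduced from the article alone. One assumed set comes close: alpha .05, no earlier R², 11 predictors tested. With λ = N × increment/(1 − R²):

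- 200 × .08/.92 = 17.4, power .792
- 200 × .09/.91 = 19.8, power .852

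Nothing in the present point turns on this. With 200 complete cases, N and the degrees of freedom are the same whichever wave supplies the scores.

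**3. Illustration of the possible size**

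The values below are assumptions, not figures from the article. Let b be the effect of the T2 score on behaviour, c the effect of behaviour on the T3 score, and s the stability of the score from T2 to T3, all standardised. Then:

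- R² using T2 scores = b²
- R² using T3 scores = (s·b + c)²

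| b | c | s | R² with T2 | R² with T3 |
|---|---|---|---|---|
| 0 | .2 | .6 | 0 | .04 |
| 0 | .3 | .6 | 0 | .09 |
| .2 | .2 | .6 | .04 | (.12 + .20)² = .10 |
| .2 | .3 | .5 | .04 | (.10 + .30)² = .16 |
| .2 | 0 | .6 | .04 | (.12)² = .014 |

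A simulation of the same set-up agreed with these values to within .002.

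**4. Chance of a significant result in the first two rows**

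Fisher z, two-sided .05, N = 200, one predictor: probability ≈ Φ(atanh(r)·√197 − 1.96).

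- r = .2: .2027 × 14.036 − 1.96 = 0.885, probability .81
- r = .3: .3095 × 14.036 − 1.96 = 2.384, probability .99

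With no forward effect, a same-wave test would thus usually be significant, and at the upper end its R² has the size of the .09 increment the article names. The last row shows the opposite error: with a real forward effect and no reverse path, same-wave scores understate it.

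**The case against.** The strongest reply is that the article never names a wave for the predictors. The words on T3 data follow the mention of the dependent variable and could describe only the outcome. This stands as a caution: same-wave predictors are the natural reading, not a stated fact. The parallel sentence about T4 data favours that reading, and nothing points to T2. On the narrower reading the predictor wave is open among several, and the same sentence would settle it.

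Second, objective 2 asks for variables independently associated with thorough self-examination, and same-wave models can answer that. This stands too. The mismatch is with the main objective, hypothesis 2 and the Discussion.

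Third, using T2 scores is not a clean cure. The article does not say whether the T2 scales are completed before or after the education session. Pre-session knowledge or self-efficacy may differ from the level held during months 0 to 3. T2 scores may reflect earlier self-examination, and T3 scores used for T4 carry the effect of practice in months 0 to 3. These points stand and shape the fix.

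A reader might also infer that the longitudinal design goes unused. The document does not support that: hypothesis 1 compares the first three months with months 9 to 12.

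**Conclusion.** The point holds in a limited form. On the natural reading, blocks 2 to 6 are measured at or after the end of the behaviour they are meant to predict, although the same constructs are scheduled at T2. The resulting models support statements of association, but not of prediction or of factors that affect later practice.

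The size is unknown. The R² of .04 to .09 and the probabilities of .81 to .99 rest on an assumed absence of forward effect, an assumed reverse correlation of .2 to .3, and a single-predictor test. The plan would test self-efficacy, for example, only after sex, knowledge and attitude. A reader might take these probabilities as the study's false-positive rate; the documents give no basis for that. Nor is any figure in the article shown to be wrong. This is an inexpensive improvement to the analysis.

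Separately, Measures refers to "SSE behaviors during the first 3 months (T1) and 12 months (T2) after dermatological education", whereas the rest of the article calls these time points T3 and T4. This is an evident slip and adds no weight to the main point.

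**What to change.** In Data analysis, objective 2:

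1. State that blocks 2 to 6 use T2 scores for the T3 outcome.
2. For the T4 outcome, choose T2 or T3 scores in advance and run the other as a sensitivity analysis.
3. Adjust for earlier self-examination: past practice from T1 in all lagged models, and T3 self-examination when T3 scores predict T4. The T1 scale is described as covering practice before the current diagnosis, so some confounding by practice between diagnosis and T2 may remain and should be acknowledged.
4. Keep same-wave models as secondary and report them as associations only.
5. State whether the T2 scales are completed before or after the education session, and interpret the coefficients accordingly.
6. As an editorial correction, align the T1/T2 labels in Measures with T3/T4.

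The cost is wording and a few more model terms. All the scales are already scheduled, and the power statement is unchanged for a given R² increment and number of tested predictors, apart from the few degrees of freedom used by the adjustment. The main downside is that lagged associations are usually weaker than concurrent ones, so a smaller increment may have to be expected.

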### Facilitating skin self-examination

Even though cutaneous melanoma are readily visible on the skin surface and it is well-known that SSEs are related to better prognosis [32,40,41,43,44], most melanoma survivors do not perform systematic skin exams regularly [27,34,45,46]. These observations have prompted research efforts to determine factors that may influence whether SSE is performed. Studies have shown, for instance, that having a personal or family history of skin cancer [40] is related to SSE. Demographic characteristics associated with SSE in the general population as well as in melanoma survivors include being female and having a higher level of education [27,40,45]. Unlike medical and demographic factors linked to SSE, which are not generally amenable to intervention, psychosocial and educational factors associated with SSE are potential targets of interventions to improve adherence to SSE instructions. Psychosocial and educational factors associated with SSE behaviors in melanoma survivors and other high-risk individuals include greater knowledge about melanoma and SSE [40,47,48], higher perceived susceptibility [40,49], positive attitude towards SSE [40,50], confidence in being able to perform an efficacious skin self-exam [40,48-50], and being comfortable with having one’s partner assist in SSE [51,52]. There is also preliminary evidence that the level of anxiety and the psychosocial strain resulting from a melanoma diagnosis affect self-exam practice [53]. Furthermore, being informed about SSE by a health care professional has been shown to be associated with SSE performance [45,50,54,55], and several intervention studies in high-risk populations have reported improvement of SSE after standardized dermatological education [50,56,57]. However, improved SSE was documented for only 37% to 63% of the participants of these studies. Longer term effects of the dermatological education could not be determined as the follow-up period only ranged from 3 to 6 months in these studies. Furthermore, little is known about the patients who do not respond to dermatological education. Given that existing interventions to improve SSE have had limited success, it is important to better understand the degree to which patients adhere to SSE and to identify potentially modifiable factors that may influence adherence.

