### Study objectives

The main objective of this study is to identify short- and long-term predictors of SSE after providing best-practice clinical care, which includes medical advice on SSE, and to better understand challenges and opportunities for secondary prevention of melanoma in high-risk individuals. Specific objectives include:

(1) To determine the extent of thorough SSE performance, defined in terms of completeness and frequency, at 3 months (i.e., Endpoint 1) and at 12 months (i.e., Endpoint 2) after receiving a standardized dermatological education session on SSE during melanoma follow-up care.

(2) To identify psychosocial variables, including distress, coping strategies, and physician and partner support that are independently associated with thorough SSE at 3 months and at 12 months following a standardized dermatological education session.

(3) To use qualitative methods to understand psychosocial factors, including physician and spousal support of SSE (or lack thereof), that help patients to affectively, cognitively and behaviorally adjust to the melanoma diagnosis and to the continuous need for SSE.

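### The objective 2 regressions adjust for sex but not for education, which the protocol names as a correlate of SSE and collects, so the independent associations are open to confounding by education

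*Protocol article*

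**What the plan says.** Study objectives, item 2, sets the target: variables "independently associated with thorough SSE at 3 months and at 12 months".

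The Background section on facilitating SSE says that demographic correlates of SSE, in the general population and in melanoma survivors, "include being female and having a higher level of education". It then contrasts demographic and medical factors, which it regards as mostly beyond the reach of intervention, with psychosocial and educational factors, which it regards as potential targets.

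In the Measures section, the sociodemographic form "includes questions about age, sex, education, having a spouse, socioeconomic status, and cancer diagnosis".

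The Data analysis section, under objective 2, sets the linear model for completeness: "The independent variables described above will be entered block-wise, i.e., 1^st^ block: sex". Knowledge and attitude are block 2, self-efficacy is block 3 and skin cancer-specific distress is block 4. The list ends with "5^th^: partner support and physician support; 6^th^: total score of the coping measure". That makes eight predictors, with sex the only demographic one.

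For frequency, "a multinomial regression will be conducted with the same predictor variables and SSE frequency". For 12 months, "The strategies described for T3 will be repeated using the data collected at T4". An optional composite outcome would use similar regressions.

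**The concern.** The protocol names two demographic correlates of the outcome. One enters the model. The other is collected and then left out of a list that is introduced as complete and covers all six blocks.

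If better-educated patients also differ in knowledge, attitude, self-efficacy, distress, support or coping, the coefficient of that variable takes up part of the education effect. The association would then be reported as independent when it partly stands in for education.

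This matters for the use planned in the Discussion section, where the results are to be the basis of a tailored psychosocial intervention. A variable that merely marks education would look like a modifiable target, although the Background places demographic factors among those that intervention cannot generally change.

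**Working it through.** **1. The plan's own figure.** The Data analysis section gives power .79 for an R² increment of .08 and .85 for .09 at N = 200. The significance level, the number of tested terms and the R² of earlier blocks are not given, so the figures can be matched but not confirmed.
- Formula: f² = ΔR²/(1 − R²_full) and λ = N·f², referred to a noncentral F distribution.
- With no earlier variance, λ = 200 × .08/.92 = 17.4 and 200 × .09/.91 = 19.8.
- At alpha .05 with 11 tested degrees of freedom, power is .791 and .852, which matches. Other unstated combinations match as well.

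The figure does not bear on the confounding itself. It is used below to price the fix.

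**2. Inputs for the confounding check.**
- From the protocol: N = 200, and eight predictors (sex plus seven others).
- Assumed, because the documents give no value: correlation r between education and an affected predictor, .2 to .3; standardised effect β of education on SSE, .15 to .30; number k of the seven non-sex predictors related to education, 3 to 7. These predictors are related to each other only through education (pairwise correlation r²) and have no effect of their own.

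**3. Formulas, with education omitted.**
- Bias of each affected coefficient: b = βr / [1 + (k − 1)r²].
- Variance picked up by the k predictors together: R² = kβ²r² / [1 + (k − 1)r²].
- Variance inflation: V = [1 + (k − 2)r²] / {(1 − r²)[1 + (k − 1)r²]}.
- SE = √[(1 − R²)V/191], where 191 = 200 − 8 − 1.
- The false-positive rate is the two-sided 5% rejection rate of a noncentral t with shift b/SE.

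**4. The two ends of the range.**
- r = .2, β = .15, k = 7: b = .03/1.24 = .024, SE = .0725, shift .33, rejection 6.3%.
- r = .3, β = .30, k = 3: b = .09/1.18 = .076, SE = .0721, shift 1.06, rejection 18.3%.

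| r | β | k = 3 | k = 7 |
|---|---|---|---|
| .2 | .15 | 6.7% | 6.3% |
| .2 | .20 | 8.0% | 7.3% |
| .2 | .30 | 12.0% | 10.3% |
| .3 | .15 | 8.2% | 6.8% |
| .3 | .20 | 10.7% | 8.3% |
| .3 | .30 | 18.3% | 12.7% |

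A simulation of the full eight-predictor model (6,000 data sets per setting) agreed to within 0.4 percentage points. With education added, the rate was 4.7% to 5.3% throughout.

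**5. If earlier blocks carry part of the education effect.** Take β as the total effect of education, with knowledge, attitude and self-efficacy each correlated .3 with it. A later null predictor is then rejected as follows:
- none of the effect runs through them: about 6% to 18%;
- half does: 5.3% (r = .2, β = .15), 6.7% (r = .3, β = .20), 8.6% (r = .3, β = .30);
- all does: about 5%.

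**6. Size against the planned effect.** At r = .3 and β = .30, one affected predictor alone would pick up .09² = .008 of R². A two-variable block would pick up 2 × .0081/1.09 = .015. Both are well below .08. If r = 0 there is no bias.

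**7. Price of adjustment.** Under the matching assumptions in step 1, power for an increment of .08 goes from .7914 to .7913 with one added degree of freedom and .7909 with four. For .09 it goes from .8520 to .8519 and .8515.

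**The case against.** The best defence is that block 1 follows hypothesis 2, which says that sex predicts SSE and that psychosocial variables explain variance beyond that. The planned blocks test exactly this, and each predictor is adjusted for the others. That explains why sex comes first. It does not explain why the other named demographic correlate is absent from a model meant to show independent association. A sex-only first step keeps the hypothesis intact.

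It can also be said that a journal article condenses a fuller plan, and that the Data analysis section promises additional analyses, including interactions and subsample differences. But the article does not defer the adjustment set. It states it as a numbered, closed list. The additional analyses name no adjustment for education.

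Three points on the other side stand. First, no passage links education to distress, support, self-efficacy or coping, so a reader who concludes that the associations are confounded goes beyond the documents. Second, knowledge, attitude and self-efficacy enter before distress, support and coping, and may absorb part of the education effect for those later variables. They offer no such protection to themselves, since they are tested predictors too. Third, the Background passage names education, not age, time since diagnosis or melanoma stage. Enrolment within 12 months of diagnosis also limits the range of time since diagnosis. A reader might infer that all of these must be in block 1, but the protocol's own premises do not require it.

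**Conclusion.** The point holds for education. The protocol names it as a correlate of the outcome, collects it, and leaves it out of every objective 2 model, so independence from it is not secured.

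Under the assumed values, the false-positive rate for an individual null predictor is about 6% to 18% instead of 5%, and about 5% to 9% if half of the education effect runs through knowledge, attitude and self-efficacy. The block tests against an increment of .08 are little affected. The exposure lies in the tests of individual variables, which objective 2 is about and which the Data analysis section says will be examined.

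A reader might infer higher rates from a model with education related to one predictor only. The formula above with k = 1 gives 7.0% (r = .2, β = .15) to 23.7% (r = .3, β = .30). Nothing in the documents supports singling out one predictor in that way, and the range for three to seven affected predictors is the fairer guide to the planned analysis. All these rates rest on assumed correlations, and the calculations cover the linear model only.

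**What to change.** In the Data analysis section, under objective 2, enter sex as the first step, so that hypothesis 2 is tested as stated. Enter education level as the second step, before the knowledge and attitude block. Use this order in the linear model for completeness and the multinomial model for frequency, at 3 and at 12 months, and in any composite model. If education is to stay out of the main models, give the reason and add a sensitivity analysis that includes it.

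The cost is one sentence and no new data. The linear model spends one degree of freedom, or a few if education is categorical, with negligible loss of power. The three-category multinomial model spends twice as many: with one to four terms for education, 2 to 8 slopes on top of the 16 already planned. Education should therefore be coded sparingly there. Partner questions go only to participants with a spouse, so the models from block 5 on may have fewer than 200 complete cases, which is a further reason for sparing coding.

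Age, time since diagnosis and stage may be added in a sensitivity model. That is optional.
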